**Conclusions:**

There are no studies to date comparing ultrasound guided fascia iliaca block with spinal morphine for pain control after hip arthroplasty. If the ultrasound guided fascia iliaca block provides pain relief which is not inferior to spinal morphine, then morphine could be removed from the spinal injection. This could reduce side effects and improve patient safety.

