## Background

Hip surgery is increasingly being performed, often in elderly patients with significant co-morbidity [1]. Whilst the optimal anaesthetic technique is yet to be established [2], it is important that side effects are minimised to optimise patient safety and comfort and to facilitate rehabilitation. The main anaesthetic options are general anaesthesia (GA) and regional anaesthesia (RA) or a combination of the two. In a recent systematic review, regional anaesthesia (RA) was demonstrated to reduce post-operative pain, morphine consumption and nausea and vomiting compared to systemic analgesia [3].

Spinal anaesthesia is a RA technique commonly used in many patients undergoing hip arthroplasty [4]. Opioids are frequently added to the spinal anaesthetic in order to prolong and improve post-operative pain relief [5] and are associated with reduced post-operative morphine requirements in patients undergoing hip arthroplasty [6-8]. However, intrathecal opioids are associated with side effects including urinary retention, nausea and vomiting, pruritus and rarely, but most seriously, respiratory depression [9]. Such adverse effects can be uncomfortable for the patient, delay mobilisation, recovery and eventual discharge and occasionally be dangerous [10,11].

In patients undergoing hip arthroplasty peripheral nerve blockade has been shown to improve pain scores and reduce morphine consumption [3]. The fascia iliaca nerve block can provide sensory blockade of the main nerves which supply pain to the hip [12,13]. However, clinical success rates of this block when performed 'blindly' using traditional landmark techniques are variable [14]. Using ultrasound to locate nerves during peripheral nerve blockade has repeatedly been shown to increase success rates, reduce block onset time, increase block duration, reduce volumes of local anaesthetic required and increase patient satisfaction compared to traditional techniques [15-21]. The use of ultrasound guidance in the fascia iliaca plane block has been shown to increase success compared with the landmark technique [22]. In this study however, the clinical benefits of this increased success were not investigated.

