### Objectives and Outcome Measures

This study aims to compare the efficacy and safety of ultrasound guided fasca iliaca block with intrathecal morphine in the provision of post-operative analgesia after primary hip arthroplasty. The primary outcome measure is post-operative morphine consumption in a 24 hour period as self administered using a patient controlled analgesia (PCA) pump. Secondary outcomes include pain scores at 3, 6, 12, 24, 36 and 48 hours, time to 1st morphine administration, episodes of respiratory depression, hypotension, nausea and vomiting scores, pruritus scores, sedation scores, urinary retention, time to first mobilisation and patient satisfaction.

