### Randomisation

A computer generated allocation sequence (in permuted blocks) will be created by an independent operator who is not directly involved with the study. Once created, the allocation sequence will be kept in a secure locked drawer making it inaccessible to all study personnel. Allocation concealment will be achieved using sequentially numbered sealed envelopes which are opaque when held to the light. When a patient is enrolled in the study, an administrator working within the Glasgow University Academic Unit of Anaesthesia will be contacted and asked to give the next numbered envelope to the anaesthetist who will make up the medications used in the study. The administrator will record the patient's details and the number of the envelope assigned to that patient. The allocation sequence will be accessed only when study data collection is complete or in any instance where unblinding of the study is thought to be essential in the provision of appropriate patient care.

Patients in the *Fascia Iliaca Group *will receive; spinal anaesthesia with hyperbaric bupivacaine at a dose between 10 and 15 mg, adjusted based on patient height and weight at the discretion of the attending anaesthetist, with no spinal morphine (0.1 ml sterile saline will be administered in its place). Ultrasound guided fascia iliaca block using 2 mg/kg levobupivacaine diluted to a total of 40 ml with sterile saline.

Post-operative analgesia will include Paracetamol 1 g four times daily and patient controlled analgesia (PCA) with morphine (1 mg bolus, 5 minute lockout period).

Patients in the *Spinal Morphine Group *will receive; spinal anaesthesia with hyperbaric bupivacaine as above, and with the addition of intrathecal morphine 100 micrograms (0.1 ml). "Sham" ultrasound guided fascia iliaca injection with 40 ml of sterile saline. Post-operative analgesia in the same manner as in the *Fascia Iliaca Group*.

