The null Hypothesis (H0) for this non-inferiority study is that the experimental treatment (ultrasound guided fascia iliaca block) is in fact inferior to the established treatment (spinal morphine) by more than the clinically significant amount (δ*). If H0 is rejected, the alternative hypothesis is that ultrasound guided fascia iliaca block is not inferior to IT opioid.

The study will be performed using both intention to treat and "as treated" analyses. In the intention to treat analysis, patients will be considered failures if they require general anaesthesia, or were unable to receive randomised treatment for any other reason. In the "as treated" analysis, only data from patients completing randomised treatment will be analysed.

Secondary data analyses will be carried out on all secondary outcomes. These will be compared between groups using t-test, and Mann-Whitney, or Chi-squared tests as appropriate.

It is anticipated that recruitment for this study will take between 12 and 18 months to complete if 1 to 2 patients are enrolled each week, using one surgeon to reduce surgical variability. Data collection for each patient will occur during the first 48 hours post-operatively and at a routine 6 week follow up appointment. No further follow up will be routinely arranged. Any patients requiring specific follow up will have this arranged on an individual basis.

We recognise that while this study is powered for the primary outcome, it is not powered for the secondary outcomes. However, the data we collect in this study will provide useful information for further studies looking specifically at these outcomes.

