## Discussion

### Risk Benefit Assessment

We expect that all patients will benefit from this study in view of the high level of post-operative monitoring and follow up which will be employed. In order to achieve blinding and improve the validity of the study, a "sham" ultrasound guided fascia iliaca block will be performed in patients in the *Spinal Morphine Group*. These patients will therefore receive an injection of an inactive substance (sterile saline) into the groin. As no local anaesthetic is being used in the sham block, potential risks will include; discomfort on injection, bleeding or bruising at the puncture site and nerve damage. Nerve damage is rare with fascia iliaca blocks as the needle is not directed towards the nerves themselves, but rather to lie in a plane between muscle layers. In the patients receiving fascia iliaca block with local anaesthetic, the risks are as before with the addition of local anaesthetic toxicity, although a pre-determined safe dose of local anaesthetic is being used.

Patients in the *Spinal Morphine Group *will receive intrathecal morphine. Spinal opioids have been used since 1979 to provide pain control after surgery [26]. Due to its widespread international use, intrathecal morphine has been extensively investigated in this setting and spinal morphine in combination with systemic morphine is a commonly used post-operative regime for many surgical procedures including hip arthroplasty [27-29]. Low dose intrathecal morphine can provide adequate analgesia whilst minimising side-effects [6-8]. Such side-effects include; delayed respiratory depression, pruritus, post-operative nausea and vomiting and urinary retention [5,30-32]. Although respiratory depression is rare with low doses of intrathecal morphine, [33] it is potentially life-threatening. Furthermore, the concomitant use of systemic opioids for post-operative analgesia may add to this risk. Previous research has concluded that 100 micrograms of intrathecal morphine combines analgesic efficacy whilst minimising the side effect profile [6,8]. Reassuringly, in a dose-finding study of intrathecal morphine for hip and knee surgery, there was no increased incidence of respiratory depression or hypoxaemia in patients receiving up to 0.3 mg of intrathecal morphine. This included elderly patients who had also received "significant doses of PCA morphine" [7].

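### The safety outcomes include none of the block harms the plan names, and the sham injection removes needle harms from the between-arm comparison

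*Protocol article*

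**What the plan says.** Objectives and Outcome Measures gives a double aim: "This study aims to compare the efficacy and safety of ultrasound guided fasca iliaca block with intrathecal morphine". After pain scores and time to first morphine, the secondary outcomes listed there are "episodes of respiratory depression, hypotension, nausea and vomiting scores, pruritus scores, sedation scores, urinary retention, time to first mobilisation and patient satisfaction". Sample Size and Statistical Considerations adds that "Secondary data analyses will be carried out on all secondary outcomes", with between-group tests, and concedes that the study is not powered for them.

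The plan describes the harms of each technique elsewhere:

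- **Spinal morphine.** Background says that "intrathecal opioids are associated with side effects including urinary retention, nausea and vomiting, pruritus and rarely, but most seriously, respiratory depression". Risk Benefit Assessment repeats these four effects.
- **Sham block.** Under Risk Benefit Assessment, "potential risks will include; discomfort on injection, bleeding or bruising at the puncture site and nerve damage".
- **Active block.** In the same section, "the risks are as before with the addition of local anaesthetic toxicity".

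Under Randomisation, the control arm receives 40 ml of saline in the groin under ultrasound. Block harms are collected outside the outcome list. Postoperative management has nerve symptoms sought at six weeks, Adverse Event Reporting and Safety has all adverse events recorded and reviewed monthly, and the end of Risk Benefit Assessment has procedure-related events recorded. The Conclusions of the Abstract say of removing morphine from the spinal injection: "This could reduce side effects and improve patient safety".

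**The concern.** The article prints a safety aim, an outcome list and a risk list, and the three do not match. The harms of the technique to be removed are well represented among the outcomes. The harms of the technique to be added, which the authors themselves name, are absent.

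A table of adverse events by arm would not fully close the gap. On the plan's own account the sham carries the same needle risks as the active block, so a between-arm difference is blind to them. The practice question is block without spinal morphine against spinal morphine without a block, and there only one side has a groin injection. A reader who took the trial's between-arm safety difference as the safety consequence of changing practice would count opioid harms avoided and leave out the needle harms added.

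**Working it through.** **1. Listed adverse effects against named harms.**

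| Harm | Named in the plan for | Listed secondary outcome? | Expected between-arm contrast |
|---|---|---|---|
| Respiratory depression | Spinal morphine | Yes | Yes |
| Nausea and vomiting | Spinal morphine | Yes | Yes |
| Pruritus | Spinal morphine | Yes | Yes |
| Urinary retention | Spinal morphine | Yes | Yes |
| Hypotension, sedation | Neither side-effect list | Yes | Either direction |
| Discomfort on injection | Block and sham | No | About zero |
| Bleeding or bruising | Block and sham | No | About zero |
| Nerve damage | Block and sham | No | About zero |
| Local anaesthetic toxicity | Active block only | No | Yes |

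Of the six listed adverse effects, four match the spinal-morphine list and none matches the block list.

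**2. Size of the arms.** The plan gives 108 in total and does not state the allocation ratio, so 1:1 is assumed. The total can be approximately reproduced. The inputs are a margin of 10 mg, an SD of 17.6 mg, a difference of 1.6 mg taken against the block, one-sided α of 0.05, and power of 0.8 (the text prints 0.8 as β):

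n per arm = 2 × [17.6 × (1.645 + 0.842) / (10 − 1.6)]² = 54.28, or 108.57 in total.

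This is used only to set about 54 per arm.

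**3. What the sham does to needle harms.** The documents give no rates, so 5%, 10% and 20% are assumptions covering bruising, discomfort and nerve symptoms together. The plan calls nerve damage rare, so these rates do not describe that component alone.

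| Assumed rate | Expected events per arm (54 × rate) | Expected difference in the trial | Difference in practice, block v no block |
|---|---|---|---|
| 5% | 2.7 | 0 | 5 points |
| 10% | 5.4 | 0 | 10 points |
| 20% | 10.8 | 0 | 20 points |

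**4. What pooling offers.** With no events in n patients, the exact one-sided 95% upper limit is 1 − 0.05^(1/n):

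- n = 54: 1 − 0.05^(1/54) = 5.4%
- n = 108: 1 − 0.05^(1/108) = 2.7%

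Pooling all injected patients halves the limit and estimates the quantity that matters for practice, the absolute rate after the injection.

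**5. Local anaesthetic toxicity.** This is the one named harm confined to the active arm, so a by-arm report is informative, but a test is not. At 54 per arm, 5 events against 0 gives a two-sided Fisher p of 0.057 and 6 against 0 gives 0.027. If the control rate is zero, power is about 5% at a true rate of 5%, 46% at 10% and 84% at 15% (all assumed rates). The added outcomes can only be descriptive.

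**The case against.** The strongest reply is that nothing is lost. Nerve symptoms are sought in both arms, all adverse events are recorded, and a table can be written later. The outcome list is introduced as what the outcomes include, so it need not be exhaustive; the statistics section does not confine analysis to listed outcomes; and a journal article commonly leaves adverse event tabulation to the full protocol or analysis plan. The sham is a disclosed cost of blinding, and the trial claims no power for secondary outcomes.

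Much of this stands. The gap is not in collection, the sham is not an error, and no one can say from this document that block harms would go unreported. What remains is that the article states a safety aim and prints both a risk list and an outcome list, yet carries none of the block risks into the outcomes. A routine by-arm table, whenever written, would still not show what the injection adds. Lack of power does not answer this, because the need is for description with intervals.

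A reader might go further and infer that the trial can hardly find against the block on safety. The documents do not support that. Both arms have PCA morphine. A block that underperforms could raise its use, and Risk Benefit Assessment says concomitant systemic opioids may add to the risk of respiratory depression. Respiratory depression, sedation, nausea and pruritus are all listed and could worsen in the block arm. Hypotension and time to first mobilisation could also go against it.

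Nor is the sentence in the Abstract a planned safety conclusion. It is a rationale, conditional on non-inferiority and hedged with a could.

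**Conclusion.** The point holds in a limited form. None of the four block harms named by the plan is a listed outcome, and no analysis of them is stated. For three of the four, the sham makes the expected between-arm difference about zero, whatever their true rate. The trial's safety contrast therefore cannot show the needle harms that replacing spinal morphine with a block would add in practice. It can still show other disadvantages of the block, so it is incomplete rather than incapable of an unfavourable result.

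This rests on the plan's own statement that sham and active block share the needle risks, on 1:1 allocation, and on spinal-morphine patients outside the trial having no groin injection. The harm rates in the illustration are assumed. The matter affects how safety is reported and worded; it leaves the primary non-inferiority comparison untouched.

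**What to change.** - Name local anaesthetic toxicity, nerve symptoms, bleeding or bruising, and discomfort on injection as descriptive secondary safety outcomes, drawn from the adverse event records and the six-week visit already planned.
- Report local anaesthetic toxicity by arm.
- Report needle harms by arm and also pooled over all injected patients, as an absolute rate with an exact confidence interval. The by-arm figures let a reader check whether pooling is reasonable. Nerve symptoms should carry the caution that all patients also have a spinal injection and hip surgery, so not every symptom is due to the groin injection.
- State that the between-arm safety difference excludes needle harms because controls had a sham injection, and that any statement about improved patient safety must weigh the pooled rate against the opioid harms avoided.

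The cost is a few lines of text and one table, with no extra patients, visits or procedures. The drawback is wide intervals for rare harms, which should be stated: even with no events among all 108, a rate of up to 2.7% could not be excluded (one-sided 95% limit).

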### Study centre

Our centre is a tertiary referral facility for orthopaedics and trauma surgery with the necessary type and volume of clinical cases required for this study. There is a wealth of experience on the use of ultrasound guidance for regional anaesthetic techniques, including fascia iliaca block [22], within the department.

### Patients and enrolment

Patients scheduled to undergo unilateral primary hip arthroplasty will be invited to participate in the study during their routine pre-assessment visit two weeks prior to the date of surgery. Inclusion criteria are; ASA physical status I - III, 18 - 85 years of age, weight between 50 - 110 kg, and competence to consent. Exclusion criteria are; contraindications to fascia iliaca plane block or spinal anaesthesia such as coagulopathy, malignancy or infection in the inguinal area, preference for general anaesthesia, allergy to opioids, significant peripheral neuropathy or neurological disorder affecting the lower extremity, pregnancy, history of alcohol or drug dependency, history of long term strong opioid intake (i.e. WHO step 3 analgesics), and history of significant psychiatric conditions that may affect patient assessment.

All suitable patients will be given a patient information sheet approved by the West of Scotland Ethics Committee. They will be given an opportunity to review this before written informed consent is obtained prior to surgery.

### Consent

The process of consent will be in accordance with the Declaration of Helsinki. Patients will be fully informed that they are being asked to participate in a research study. The procedures involved in the study, and the chances of being assigned randomly to one of two groups will be explained in person and via an information sheet. A signed, consent form will be obtained from each patient and retained by the investigators. Patients will be made aware of their right to withdraw from the study at any time without adverse effects on their clinical care.

### Randomisation

A computer generated allocation sequence (in permuted blocks) will be created by an independent operator who is not directly involved with the study. Once created, the allocation sequence will be kept in a secure locked drawer making it inaccessible to all study personnel. Allocation concealment will be achieved using sequentially numbered sealed envelopes which are opaque when held to the light. When a patient is enrolled in the study, an administrator working within the Glasgow University Academic Unit of Anaesthesia will be contacted and asked to give the next numbered envelope to the anaesthetist who will make up the medications used in the study. The administrator will record the patient's details and the number of the envelope assigned to that patient. The allocation sequence will be accessed only when study data collection is complete or in any instance where unblinding of the study is thought to be essential in the provision of appropriate patient care.

Patients in the *Fascia Iliaca Group *will receive; spinal anaesthesia with hyperbaric bupivacaine at a dose between 10 and 15 mg, adjusted based on patient height and weight at the discretion of the attending anaesthetist, with no spinal morphine (0.1 ml sterile saline will be administered in its place). Ultrasound guided fascia iliaca block using 2 mg/kg levobupivacaine diluted to a total of 40 ml with sterile saline.

Post-operative analgesia will include Paracetamol 1 g four times daily and patient controlled analgesia (PCA) with morphine (1 mg bolus, 5 minute lockout period).

Patients in the *Spinal Morphine Group *will receive; spinal anaesthesia with hyperbaric bupivacaine as above, and with the addition of intrathecal morphine 100 micrograms (0.1 ml). "Sham" ultrasound guided fascia iliaca injection with 40 ml of sterile saline. Post-operative analgesia in the same manner as in the *Fascia Iliaca Group*.

### Blinding

The ultrasound guided fascia iliaca block will be performed by an anaesthetist deemed competent in this technique. The injectate solutions will have been pre-prepared in an aseptic manner by a separate anaesthetist not involved with post-operative data collection or analysis. In this way, the investigator performing the ultrasound guided fascia iliaca block and spinal injections will be blinded to the nature of the injectates. As patients will receive both spinal and ultrasound guided fascia iliaca injections, they will also be blinded. Data will be anonymised and collected by an investigator who is blinded to the patient's allocation.

### Intra-operative management

The anaesthetist looking after the patient in theatre will play no part in data analysis and will record the intra-operative proceedings as normal. The patient's participation in this study and the 2 possible anaesthetics that may have been administered will be documented on the anaesthetic chart. The randomisation code may be accessed if deemed necessary in the provision of optimal patient care. The patient may receive sedation if requested and as directed by the anaesthetic doctor. Fluid administration and the use of vasopressors will again be at the discretion of the anaesthetic doctor. All medications, with the exception of the medications used to perform the spinal or fascia iliaca block, will be detailed in the anaesthetic record. No anti-emetic will be administered peri-operatively unless specifically indicated.

### Postoperative management

After surgery, patients will be taken to the recovery room and monitored according to standard hospital policy. Pain will be treated, if required, with intravenous morphine every 5 - 10 min as directed by nursing staff. Patients will be familiarised with the Patient Controlled Analagesia (PCA) device and discharged once recovery room discharge criteria have been met. Patients will remain on oxygen for at least 24 hours and whilst receiving PCA morphine as is routine in our unit. Naloxone will be prescribed for sedation or respiratory depression as specified on the PCA protocol.

After a 48 hour period, data regarding pain scores, nausea, itch, sedation and hypotension will cease being collected as detailed in the primary and secondary outcomes. The investigator who collects the data will be blinded as to the nature of the anaesthetic administered. The time to first mobilisation will be assessed and the patient will continue to be monitored by physiotherapy staff until discharge. Any serious adverse events will prompt follow up. Patients will be seen routinely at 6 weeks following discharge by the arthroplasty specialist nurse. Symptoms of nerve damage will be actively sought at this consultation. Patients will be asked to rate their level of satisfaction with post-operative analgesia at both 48 hour and 6 week time points.

